## Abstract

**Background:**

Children in Sub-Saharan Africa (SSA) are burdened by significant unmet mental health needs, but this region has limited access to mental health workers and resources to address these needs. Despite the successes of numerous school-based interventions for promoting child mental health, most evidence-based interventions are not available in SSA. This study will investigate the transportability of an evidence-based program from a developed country (United States) to a SSA country (Uganda). The approach includes task-shifting to early childhood teachers and consists of professional development (five days) to introduce strategies for effective behavior management and positive teacher-student interactions, and group-based consultation (14 sessions) to support adoption of effective practices and tailoring to meet the needs of individual students.

**Methods/Design:**

The design of this study is guided by two implementation frameworks, the Consolidated Framework for Implementation Research and the Teacher Training Implementation Model, that consider multidimensional aspects of intervention fidelity and contextual predictors that may influence implementation and teacher outcomes. Using a cluster randomized design, 10 schools in Uganda will be randomized to either the intervention group (five schools) or the waitlist control group (five schools). A total of 80 to 100 early childhood teachers will be enrolled in the study. Teacher utilization of evidence-based strategies and practices will be assessed at baseline, immediate post-intervention (six months after baseline), and at seven months post-intervention (during a new academic year). Fidelity measures will be assessed throughout the program implementation period (during professional development and consultation sessions). Individual teacher and contextual factors will be assessed at baseline. Data will be collected from multiple sources. Linear mixed-effect modeling, adjusting for school nesting, will be applied to address study questions.

**Discussion:**

The study will produce important information regarding the value of an evidence-based early intervention, and a theory-guided implementation process and tools designed for use in implementing early childhood evidence-based programs in SSA countries or resource-constrained community settings.

**Trial registration:**

This trial was registered with ClinicalTrials.gov (registration number: NCT097115) on 15 May 2013.

## Background

Children in Uganda make up about half (56%) of the total population (compared to 20% in the United States) [1], and face many physical, mental health and educational challenges [1, 2]. Most Ugandan children live in disadvantaged communities with high rates of chronic poverty (38%), domestic violence (30%), physical violence toward children (80%), depression (33 to 39%), malaria (70 to 80%) and HIV or AIDS (6%) [3–9]. These issues have led to a significant number of orphans, poor child mental health and numerous child welfare issues [1, 8]. Poor child mental health has been shown to be strongly related to poor physical health, low secondary education enrollment, substance abuse and violence among adults in developing countries [10–12], and has enormous consequences on the country’s economic development and international resources.

Although Uganda receives a large amount of international resources to address many child health needs, most focus on the provision of clean water, vaccinations, nutrition programs, protection and education [13]; limited attention has been given to child mental health problems. Of the available mental health interventions, most are limited to awareness or public education campaigns [14], and no attention has been paid to developing a population-based strategy to promote child mental health. This service gap is partly attributable to a lack of trained child mental health workers. Uganda, like many other developing countries, has few mental health workers (0.08 psychiatrists, 0.01 psychologists, 0.01 social workers and 0.78 nurses per 100,000 population, compared to between 10 and 60 in developed countries) [15]. Most mental health professionals are not specialized or trained in prevention services, and Uganda’s mental health policy has remained at the drafting stage since 2000 [16].

### Population-level approach to promoting child mental health

A large body of developmental research suggests that preventive interventions during early childhood can result in improved mental and physical health, academic attainment and overall wellbeing in children [17, 18]. Although numerous evidence-based preventive interventions for young children have been implemented in developed countries [17, 19–21], such mental health programs are usually not available in Uganda or Sub-Saharan Africa (SSA) [22]. Disseminating evidence-based programs (EBPs) to SSA has the potential to be a cost-efficient approach to addressing the enormous mental health needs of the pediatric population.

To have a larger public health impact and to maximize reach to the pediatric population, one strategy is to provide interventions in the school setting [23]. In Uganda, 84% of children are enrolled in primary school, with most (70%) entering at five or six years of age (Primary one) [24]. Universal intervention (for all children) in the school setting provides an opportunity to serve all students and has been shown to be an effective approach in addressing health problems (such as HIV and AIDS and poor nutrition) in SSA countries [25, 26], as well as improving child mental health in developed countries [27–30].

Given the limited number of mental health professionals in Uganda (and most SSA countries), it is not feasible to rely on such professionals to implement mental health preventive interventions (as is often the case in developed countries). Task-shifting, endorsed by the World Health Organization, offers a solution to overcoming this human resource barrier. Task-shifting involves redistributing tasks from professionally trained workers to those with less training and fewer qualifications [31, 32]. Under the right conditions (for example, political support, embedded into the community, appropriate training and coaching, remuneration and incentive systems), this approach can lead to significant health gains [33, 34]. For developing a school-based program in Ugandan schools, task-shifting involves redistributing responsibilities for implementation from mental health workers (such as social workers or psychologists) to teachers. Successful task-shifting will involve: 1) modifying the intervention to be delivered by teachers, 2) training the teachers in the mental health preventive intervention and 3) providing adequate consultation and support so that the teachers implement the intervention with fidelity. Adapting efficacious programs from developed countries to SSA countries using task-shifting also requires thoughtful consideration of individual- and system-level factors (such as leadership support, school climate and teacher characteristics) that may influence effectiveness of task-shifting or program implementation outcomes [33, 35–38]. Although some school health interventions conducted in high-income countries have suggested that leadership support, school climate and teacher characteristics may impact intervention effects [33, 35–38], we are not aware of any other studies that examine these implementation questions in African schools. The systematic study of factors that may influence implementation is necessary to develop implementation strategies to ultimately impact population health in African children.

The current protocol seeks to test a potentially cost-effective population approach to address child mental health needs in Uganda by adopting an EBP that utilizes universal prevention, task-shifting and school-focused approaches from a developed country to a SSA country (Uganda). This protocol focuses on the evaluation of the process and impact of such an implementation approach. In addition, this study will systematically examine individual and system level factors that may enhance or hinder program implementation quality and outcomes. This information is critical to the development of additional strategies to enhance task-shifting in program implementation and program outcomes.

### The mental health intervention

The EBP that we apply in this study is ParentCorps. ParentCorps is a culturally-informed, multicomponent intervention for young children that promotes high-quality learning environments at home and school (such as positive parent-child and teacher-child interactions and effective behavioral management practices), resulting in meaningful educational, developmental and health benefits for children, especially those who are behaviorally dysregulated (for example impulsive or inattentive) in early childhood [39–42]. ParentCorps was built on an extensive body of cross-cultural parenting and child developmental research [11, 39, 42–47]. The program includes three core intervention components. The ‘Professional Development’ component aims to increase knowledge, motivation and capacity to employ evidence-based practices for creating positive teacher-child interactions and strong home-school connections, and for implementing the programs for parents and students. Professional Development includes the ParentCorps ‘FUNdamentals’ course (four days large-group experiential training and two additional days of separate training for mental health professionals in implementing the ‘Program for Parents’ and teachers in implementing ‘Program for Students’) and ‘Coaching’ (providing *in vivo* support to trainees to enhance their ability to identify and address the needs of students and to employ evidence-based practices in daily interactions with students and parents). The ‘Program for Parents’ component (consisting of 14 two-hour sessions) aims to increase parent knowledge, motivation and capacity to use a set of evidence-based parenting practices (parallel to those presented in Professional Development). The ‘Program for Students’ component (consisting of 14 two-hour sessions) aims to increase children’s knowledge, motivation and capacity to use social-emotional and behavior regulation skills through lessons, activities and a systematic approach to behavior management. In two cluster (school) randomized controlled trials (RCTs) with low-income, minority students in New York City in the United States, ParentCorps has shown to be highly acceptable to ethnically diverse populations in poor urban communities, and has had significant, robust and sustained effects on all targeted teacher, parent and child outcomes [39–41, 48–50]. These include effects on teachers’ utilization of proactive and positive reinforcement strategies, positive classroom climate and confidence in engaging families (Cohen’s ds ranged from 0.42 to 0.85, comparable to the range 0.51 to 1.29 reported in the literature [51]); parents’ utilization of effective parenting practices, involvement in child education and parenting knowledge (Cohen’s ds ranged from 0.16 to 0.50, compared to 0.30 to 0.88 reported in the literature [52]); and early childhood students’ social-emotional (adaptive behaviors, externalizing and internalizing problems) and academic outcomes (Cohen’s ds ranged from 0.25 to 0.56, compared to 0.24 to 0.81 reported in the literature [52–55]).

In the United States, mental health professionals have been responsible for implementation of the Program for Parents, while teachers are responsible for the Program for Students. Using a task-shifting strategy to bring ParentCorps to Ugandan schools, the long-term plan is for Ugandan teachers to implement the Program for Parents as well as the Program for Students. A systematic series of studies with Ugandan teachers, families, school leaders, mental health professionals and policymakers and key stakeholders across Uganda indicate that the ParentCorps implementation model (Programs for Parents, Programs for Students, and Professional Development) were a good fit, and the teachers are motivated to implement both intervention components. For example, previous studies found that: 1) the task-shifting model is a familiar concept, as most schools (90%) and teachers (72%) have experience in child health promotion activities; 2) Ugandan teachers report similar mental health risk factors as those identified in other countries, including lack of parental supervision and/or involvement, negative parenting, poverty, coming from a broken home and disadvantaged home and neighborhood environments (such as slum areas and exposure to violence). Teachers also express that effective preventive strategies should include effective discipline, positive teacher-child and parent-child relationships, education of parents and children and promotion of parental involvement; 3) most teachers are interested in ParentCorps training (99%), and in providing mental health promotion activities to students and parents (97%) ([name] and [name] unpublished observations).

As the first step of transporting ParentCorps to Uganda, this initial study will focus on the teacher Professional Development component only. As in the United States, mental health professionals will provide Professional Development (ParentCorps FUNdamentals and Coaching) to implementers (in this case, teachers). This study will evaluate the feasibility of training, coaching and supporting Ugandan mental health professionals from a distance to provide Professional Development for Ugandan teachers, and estimate the impact on teacher practices.

### Conceptual framework for implementation

Figure 1 shows the theory of change model for ParentCorps implementation. Our implementation framework is adapted from Reinke *et al*.’s Teacher Training Implementation Model (TTIM) [56] and Damschroder and Lowery’s Consolidated Framework for Implementation Research (CFIR) [36]. While TTIM focuses on multidimensional aspects of intervention fidelity as related to implementation outcomes, CFIR focuses on five domains of contextual factors that may impact implementation outcomes. As per the model, fidelity (including adherence and quality of program implementation, and trainees’ engagement and exposure to the program as defined in the TTIM [56]) may impact teacher implementation of evidence-based practices in the classroom, which in turn will impact student and school outcomes. In addition, five domains of contextual predictors, derived from the CFIR [36] (including intervention characteristics, outer setting, inner setting, individual characteristics and organization process), may impact program implementation (both on fidelity and implementation outcomes) and sustainability. This study focuses on implementation processes and outcomes in the gray shaded boxes in Figure 1. Among the contextual predictors, only the school/inner characteristics (such as school leadership and climate) and individual characteristics (such as teacher factors) will be considered because of the relevance to the school contexts. This study will not focus on contextual predictors related to intervention (ParentCorps) characteristics’ because previous work shows that ParentCorps fits well within Ugandan contexts (see above).

**Figure 1 Fig1:**
[figure not shown]
**Implementation conceptual model.** This Figure illustrates the relationship among contextual predictors, implementation fidelity and implementation and child mental health outcomes.

### Implementation aims and hypotheses

***Firstly, we aim to evaluate the implementation fidelity of Professional Development*****(*****ParentCorps FUNdamentals and Coaching*****) for Ugandan teachers when implemented by Ugandan mental health professionals.** We hypothesize that Ugandan mental health professionals will implement Professional Development with high levels of fidelity.

**Secondly, within the context of an RCT, we aim to evaluate the impact of Professional Development on teacher practices in the classroom during the training school year, and during the following school year with different students.** We hypothesize that, relative to teachers in schools randomized to the waitlist control condition, teachers in intervention schools will use more effective practices in the classroom and these practices will be maintained over time and with a different student population.

**Thirdly, within intervention schools only, we aim to examine the relation between implementation fidelity, context (individual and system factors) and teacher practices.** We hypothesize that higher levels of implementation fidelity will be associated with greater use of effective practices in the classroom, and that positive school and teacher characteristics (such as better school leadership, and higher teacher self-efficacy) will predict higher teacher engagement in Professional Development and greater use of effective practices in the classroom overtime.

## Methods/Design

### Design

This study applies a matched-pair cluster randomized waitlist controlled design. To ensure approximately similar characteristics in the intervention and control conditions, a statistician unfamiliar with the study schools will match the schools based on size (number of teachers and students). Five pairs of schools will be identified. Schools will be selected from a previous study of children’s health ([name] and [name] unpublished observations), which randomly selected 30 schools from the schools registered under Ministry of Education in Kampala, Uganda. The 10 schools for the RCT will be selected from this pool of 30 schools because they all indicated interest in participation. Within each pair, one school will be randomly assigned to intervention, and the other to the waitlist control condition (receiving intervention after the RCT post-assessment). By the follow-up assessment in intervention schools, all 10 schools will have received intervention. The study has been approved by Institutional Review Boards (IRB) of New York University Langone Medical Center (IRB number: S13-00362), Makerere University (IRB number: SBS110), and Ugandan National Science and Technology (IRB number: SS3194).

### Participants

The study aims to enroll primary school and all early childhood teachers, including nursery pre-kindergarten and kindergarten, and primary one, two and three (first to third grades), serving students between four and eight-years-old. Based on our prior work, Ugandan primary schools have, on average, about 700 students (ranging from 100 to 2,300, SD = 440), 23 teachers (ranging from 7 to 56, SD = 13) and 54 students in each class (ranging from 15 to 90, SD = 21). The schools have on average six to eight early childhood teachers (for four to eight-year-olds). We anticipate that 80 to 100 early childhood teachers from the 10 study schools (40 to 50 teachers in each condition) will participate in the RCT, and estimate that more than 3,200 children across conditions (including waitlist control schools at the end of the trial) will be impacted during the study period ([name] and [name], unpublished observations). Although the trial is carried out in schools, parents, guardians and students are not considered subjects of this study. They will not participate in any research activity, therefore, consent of parents and guardians will not be obtained.

The study is being conducted by investigators from the United States and Uganda. All study recruitment and assessment procedures will be conducted by Ugandan research staff. Principals will be informed about the randomization procedures, study timeline, teacher assessments and intervention procedures (including immediate provision in the intervention schools and delayed provision in the control schools). Once principals agree to participate and sign a written agreement, teachers from the schools will be approached by research staff to assess their interest. Teachers will provide written informed consent and will be informed that they have the right to refuse to participate in the study, even though the principals and other teachers agree (with no negative consequences).

A total of 10 Ugandan mental health professionals will be recruited and trained to implement ParentCorps Professional Development. Inclusion criterion for mental health professionals is: psychologists, social workers and mental health counselors educated to at least master’s degree level,, or psychologists, social workers, counselors and psychiatric nurses educated to at least bachelor’s degree level with at least three years of clinical experience. They will be recruited from local Universities or mental health facilities. Mental health professionals who agree to participate will provide written informed consent, which will allow the research team to gather fidelity data (self-reported or observational data) from them.

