### Sample size and power

We conducted power analyses for teacher outcomes (the primary evaluation outcomes), assuming intention-to-treat analyses will be applied. Power analysis for aim three (contextual moderators) is not computed given the exploratory nature and lack of empirical evidence in this area of research. In cluster match-pair randomized designs, in addition to the usual study design parameters, the effect sizes detectable with 80% power of two-sided tests with level of significance α = 0.05 depend on the cluster (school) sizes (m), the intra-class correlation (ICC) associated with the cluster and the correlation between the schools within a pair (ρ). In technical terms, the clustering leads to a decrease of the actual sample size (N) by a factor called variance inflation factor (VIF = 1 + (m-1) ICC). The effective sample size (N*) in the case of cluster randomization is N* = N/VIF. Akin to a paired t-test, randomization within matched pairs can increase the power of a test, especially if ρ is large. Depending on the analytic model, the magnitude of the detectable effects can also be varied. For example, a model which includes covariates that account for some variance in the outcome, such as baseline levels of the outcome, would be more powerful (and would provide adequate power to detect smaller effects) than a model that does not make use of covariates [57].

We estimate the magnitude of the effects that are detectable with 10 schools, matched in five pairs, and 80 to 100 teachers (or eight to 10 teachers per school) with respect to post-intervention outcomes, at 80% power of a 2-sided test with level of significance α = 0.05. The following assumptions are made in those computations: 1) the baseline values of the outcome and other baseline covariates in the model account for 20 to 50% of variance of the post-intervention outcomes (estimated variance obtained from trials conducted in the United States); 2) correlations of the outcome measures between schools within a pair (ρ) will be high, ranging from 0.50 to 0.70; and 3) ICCs associated with clustering of teachers within a school will range from 0 to 0.10. The detectable effects (Cohen’s d) would be d = 0.11 to 0.29. The proposed study will have sufficient power to detect impact on teacher outcomes that are meaningful and realistic.

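### The protocol's average of six to eight early childhood teachers per school gives 60 to 80 teachers in 10 schools, not the 80 to 100 used for enrolment and power

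*Protocol article*

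**What the plan says.** Three places in the protocol article give the number of teachers, and one gives the number per school.

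- Participants, per school: "The schools have on average six to eight early childhood teachers (for four to eight-year-olds". The article presents this as coming from the team's prior work.
- Participants, the next sentence: "We anticipate that 80 to 100 early childhood teachers from the 10 study schools (40 to 50 teachers in each condition) will participate".
- Abstract, Methods/Design: "A total of 80 to 100 early childhood teachers will be enrolled in the study".
- Sample size and power: detectable effects are computed for "10 schools, matched in five pairs, and 80 to 100 teachers (or eight to 10 teachers per school", "at 80% power of a 2-sided test with level of significance α = 0.05".

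The Design section uses school size to form the five matched pairs: "Within each pair, one school will be randomly assigned to intervention, and the other to the waitlist control condition". It says that the 10 schools come from a pool of 30 randomly selected schools that had expressed interest. It does not say that larger schools are preferred. Participants also says that teachers are free to decline even when their principal has agreed, and gives no expected participation rate.

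**The concern.** The per-school figure and the total stand in adjacent sentences, refer to the same category of teacher, and do not multiply out. The total is also an input to the power statement, where it reappears as a cluster size of eight to 10. The bottom of that range is the top of the prior-work range.

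If the study schools resemble the schools described, the trial will enrol fewer teachers than planned, and the stated detectable effect rests on a cluster size that the article's own data do not support. Voluntary consent can only lower the number. This is not a detail that an article would leave to a fuller document, because two published figures disagree and one of them feeds a calculation.

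**Working it through.** **Inputs from the article.** 10 schools in five pairs; six to eight early childhood teachers per school (Participants); 80 to 100 teachers, eight to 10 per school (Sample size and power); two-sided α = 0.05, power 80%; R² = 0.20 to 0.50; within-pair correlation ρ = 0.50 to 0.70; ICC = 0 to 0.10; VIF = 1 + (m − 1) × ICC.

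**Step 1: the stated total.** 10 × 8 = 80 and 10 × 10 = 100, which is 40 to 50 per condition with five schools each. The total agrees with the power section's cluster size.

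**Step 2: the total from the Participants figure.** 10 × 6 = 60 and 10 × 8 = 80, which is 30 to 40 per condition. The two ranges share only the value 80. The planned number exceeds the derived one by 80/60 − 1 = 33% at the lower end and 100/80 − 1 = 25% at the upper end.

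**Step 3: effective sample size at ICC = 0.10.**

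| N | m | VIF | N/VIF |
|---|---|---|---|
| 60 | 6 | 1.5 | 40.0 |
| 80 | 8 | 1.7 | 47.1 |
| 100 | 10 | 1.9 | 52.6 |

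**Step 4: change in detectable effect, like for like.** The multiplier is 1.960 + 0.842 = 2.80. The favourable end takes the larger m, ICC = 0, R² = 0.50 and ρ = 0.70. The unfavourable end takes the smaller m, ICC = 0.10, R² = 0.20 and ρ = 0.50. The article does not print its formula, so two are shown.

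*Formula A, pairing acts on the between-school part only:* d = 2.80 × √{2(1 − R²)[ICC(1 − ρ) + (1 − ICC)/m]/5}.

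- m = 10, favourable: 2.80 × √(2 × 0.5 × 0.100/5) = 0.40
- m = 8, favourable: 2.80 × √(2 × 0.5 × 0.125/5) = 0.44
- m = 8, unfavourable: 2.80 × √(2 × 0.8 × [0.05 + 0.1125]/5) = 0.64
- m = 6, unfavourable: 2.80 × √(2 × 0.8 × [0.05 + 0.15]/5) = 0.71

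So 0.40–0.64 at m = 8 to 10 becomes 0.44–0.71 at m = 6 to 8, a rise of 12% and 11% at the two ends.

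*Formula B, pairing acts on the whole variance:* d = 2.80 × √{4 × VIF × (1 − R²)(1 − ρ)/N}.

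- N = 100, favourable: 2.80 × √(4 × 1.0 × 0.15/100) = 0.22
- N = 80, favourable: 2.80 × √(4 × 1.0 × 0.15/80) = 0.24
- N = 80, unfavourable: 2.80 × √(4 × 1.7 × 0.40/80) = 0.52
- N = 60, unfavourable: 2.80 × √(4 × 1.5 × 0.40/60) = 0.56

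So 0.22–0.52 becomes 0.24–0.56, a rise of 12% and 8.5%. At the effect that had 80% power with the planned number, power falls to about 71% (favourable end) or 73% (unfavourable end).

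**Step 5: the printed range.** Neither formula returns the article's d = 0.11 to 0.29 at 80 to 100 teachers. That is a separate issue, and the relative changes in Step 4 do not depend on it.

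**The case against.** The strongest defence is that six to eight is an average from earlier schools and not a count in the 10 study schools. Participants reports 7 to 56 teachers of all grades per school, with an SD of 13, so 10 schools drawn from 30 could average eight or more. The low end, 80, is reachable if the schools average eight and every teacher consents. This part stands: the documents do not show that 80 to 100 is impossible. What they lack is any reason to expect it, since size enters only as a matching variable.

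A reader might infer more than the text supports in five ways.

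- **That 80 is a ceiling.** An average does not bound the total in 10 particular schools.
- **That the estimate of more than 3,200 children confirms about 60 teachers**, because 3,200/54 = 59 classes. This needs one teacher per class, which the article does not state. Its own averages give 700/54 = 13 classes for 23 teachers, about 1.8 teachers per class, and on that ratio 59 classes go with about 105 teachers. The early grades may differ, so the figure supports neither side.
- **That turnover into the new school year weakens the power figure.** That figure concerns post-intervention outcomes, six months after baseline.
- **That power for maintenance or aim three is overstated.** No power is claimed for maintenance, and the article says that power for aim three was not computed.
- **That the eligible counts are already known from the matching.** Matching uses total teachers and students, not early childhood teachers.

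**Conclusion.** The point holds as an unexplained mismatch of modest size. On the article's own average, 10 schools give 60 to 80 teachers (30 to 40 per condition) before refusal, against a planned 80 to 100. This assumes that the study schools resemble those of the prior work. It takes no allowance for refusal because no rate is given; any refusal would lower the number further.

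The consequence for precision is a detectable effect about 8% to 12% larger at the same ICC, R² and ρ. It is no larger because the number of schools is unchanged. It would be tempting to set 60 teachers against 100 and report a bigger loss, but that compares opposite ends of the two ranges. Nothing here calls the design, the analysis model or the number of schools into question.

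**What to change.** Choose one of two routes and apply it in the abstract, Participants, and Sample size and power.

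1. Restate expected enrolment as 60 to 80 teachers (30 to 40 per condition, six to eight per school).
2. Or replace the range with the actual counts of eligible early childhood teachers in the 10 schools. If these support eight to 10 per school, say so and give the source.

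Either way, recompute the detectable effect with that cluster size, print the formula, and state an assumed refusal rate as an assumption.

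The cost is a few corrected figures and a slightly less favourable statement of precision. No schools need be added, and conduct and analysis do not change.
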